#### Safety outcome

2.4.4

All adverse events (AEs) occurring during the study will be comprehensively documented in the clinical research forms (CRFs), detailing the timing, symptoms, severity, interventions, prognosis, and any other relevant information. The severity of AEs will be assessed using the Common Terminology Criteria for Adverse Events (CTCAE) version 5.0 (28), as defined by the National Institutes of Health (NIH), with grades 3–5 classified as severe. The acupuncturist and study team will evaluate the potential causal relationship between the AEs and the LSM treatment. AEs potentially related to LSM may include, but are not limited to, blisters, erythema, pruritus, burns, and respiratory symptoms. Safety monitoring will involve regular assessments of the treatment site, temperature measurements to minimize the risk of burns and excessive erythema. Appropriate interventions will be implemented for all AEs, regardless of their association with LSM. In the event of severe AEs, urgent medical attention will be provided, the study intervention will be discontinued, and the research ethics committee will be notified within 24 h with a detailed report outlining the nature of the event, actions taken, and outcomes. The participant will be closely monitored until the serious AEs are adequately managed. The study team will conduct a thorough review of the severe AEs to determine whether modifications to the study protocol are necessary to prevent recurrence.

### Participant timeline

2.5

Figure 2 provides a detailed timeline outlining the schedule for participant enrollment, intervention procedures, outcome assessments, and systematic data collection throughout the study period.

**Figure 2 fig2:**
[figure not shown]
Detailed timeline of enrolment, interventions and assessments. FACT-B, Functional Assessment of Cancer Therapy-Breast; ISI, Insomnia Severity Index; LSM, long-snake moxibustion; PSQI, Pittsburgh Sleep Quality Index; PFS, Piper Fatigue Scale.

### Randomization

2.6

An independent biostatistician will generate the randomization sequence using a stratified block randomization design. Block sizes of 2 or 4 will be used, with stratification based on whether patients are currently receiving endocrine therapy (yes or no). Participants will be assigned to either the LSM or WC groups in a 1:1 ratio. The randomization codes will be sealed in sequentially numbered, opaque envelopes, which will be securely maintained by independent administrative staff. Participants will receive their envelopes in the order of enrollment to determine their group allocation.

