#### Recruitment

2.2.1

A comprehensive, multi-channel recruitment strategy will be implemented to enroll participants, utilizing posters, media advertisements, and clinical referrals. Prospective participants will undergo an initial screening through face-to-face interviews and baseline assessments conducted by the research team to confirm their eligibility for the study. In line with ethical standards, detailed information regarding the study’s objectives, intervention procedures, potential benefits, and associated risks will be provided to ensure participants give fully informed consent before enrollment.

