### Blinding

2.7

Given the distinct nature of LSM therapy, creating a placebo moxibustion is challenging. Consequently, this study will be conducted as an open-label trial, with both participants and acupuncturists aware of their treatment assignments. To mitigate potential bias, blinding will be maintained for outcome assessors, data managers, and statisticians. During assessments, outcome assessors will use CRFs containing participant names, while both participants and assessors will be instructed to avoid discussing treatment allocation. Once assessments are complete, independent administrative staff overseeing randomization will replace participant names with coded labels, and group assignments will be replaced with anonymized labels. The anonymized dataset will then be provided to data managers and statisticians for analysis. Since statisticians will only have access to the anonymized dataset, they will conduct the analysis without knowledge of treatment group assignments, ensuring unbiased interpretation of results. After data analysis is finalized, the identities associated with the codes will be disclosed to the research team for accurate interpretation of the results.

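### Blocks of 2 or 4 in an open-label, single-centre trial leave many allocations predictable to any recruiter who knows the sizes and the earlier allocations

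*Protocol article*

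**What the plan says.** The Randomization section of the protocol article has an independent biostatistician prepare the list and fixes the scheme: "Block sizes of 2 or 4 will be used, with stratification based on whether patients are currently receiving endocrine therapy (yes or no"). Allocation is 1:1. On concealment it says: "The randomization codes will be sealed in sequentially numbered, opaque envelopes, which will be securely maintained by independent administrative staff".

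The Blinding section states that "this study will be conducted as an open-label trial, with both participants and acupuncturists aware of their treatment assignments". The masked roles are named: "blinding will be maintained for outcome assessors, data managers, and statisticians". Staff who recruit are not on that list.

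Under Recruitment, screening consists of "face-to-face interviews and baseline assessments conducted by the research team to confirm their eligibility for the study". Study design gives one centre and 100 participants.

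**The concern.** Permuted blocks force the arms back to balance at the end of every block. The shorter the block, the more an imbalance so far reveals about the next allocation. In an open-label trial past allocations can become known: here one arm attends eight sessions of about 1.5 hours and the other waits. The block sizes, which would normally be kept from recruiting staff, are printed.

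A recruiter who can guess the next arm can, knowingly or not, bring forward, delay or discourage a particular patient. The arms then differ in prognosis at entry, which is what randomisation is meant to prevent. Eligibility runs from an ISI score of 8 upwards, and the primary outcome is change in that self-reported score, so there is room for such steering to matter.

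**Working it through.** The article gives no figure for predictability, so there is none to reproduce.

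**Inputs from the article.** Block sizes 2 and 4, two strata, 1:1 allocation, 100 participants.

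**Assumptions, because the article does not state them.**
- A block has size 4 with probability q; q = 0.5 is the base case and the range is shown.
- The recruiter knows both sizes and keeps a complete tally within each stratum, but does not know where each block begins.
- A stratum holds 50 participants; the result barely depends on this.

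**Step 1: how often a stratum is out of balance.** Every completed block is balanced, so any imbalance comes from the current block.
- Block of 2: only the second allocation is made from imbalance, so 1.
- Block of 4: the second and fourth always are, and the third is if the first two agree (probability 1/3), so 1 + 1/3 + 1 = 7/3.
- Long-run share = [(1 − q) × 1 + q × 7/3] / [2(1 − q) + 4q].
- At q = 0.5: (0.5 + 1.1667) / 3 = 55.6%.

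**Step 2: how certain the guess is.** The least informative imbalance follows the first allocation of a block. The other arm is then next with probability (1 − q) × 1 + q × 2/3 = 1 − q/3. At q = 0.5 this is 83.3%, so every allocation counted in step 1 passes the 80% mark. That holds up to q = 0.6, where 1 − q/3 = 0.80.

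**Step 3: certain predictions.** With mixed sizes, full certainty arises when the imbalance reaches 2. The block must then be of size 4 and its last two allocations are known. Long-run share = q × (1/3) × 2 / [2(1 − q) + 4q]. At q = 0.5 this is (1/3) / 3 = 11.1%.

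**Step 4: overall correct guesses**, always naming the lagging arm and tossing a coin when balanced.
- Block of 2: 0.5 + 1 = 1.5 correct.
- Block of 4: 0.5 + 2/3 + (1/3 × 1 + 2/3 × 0.5) + 1 = 2.833 correct.
- At q = 0.5: (0.5 × 1.5 + 0.5 × 2.833) / 3 = 72.2%, against 50% by chance.

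**Step 5: simulation** of a guesser who updates the exact probabilities after each allocation, stratum of 50, sizes within each scheme equally likely unless stated:

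| Scheme | Predictable at ≥80% | Certain | Correct overall |
|---|---|---|---|
| 2/4, equal mix | 55% | 11% | 72% |
| 2/4, two thirds size 4 | 48% | 13% | 71% |
| All size 4 | 32% | 32% | 70% |
| All size 2 | 50% | 50% | 75% |
| 4/6, equal mix | 27% | 6% | 69% |
| 4/6/8, equal mix | 23% | 2% | 68% |

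For an equal mix of 2 and 4, strata of 20 to 80 participants give 55.1% to 55.4% at the 80% mark.

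**The case against.** The strongest reply is that the headline share is conditional. It needs a recruiter who knows the sizes and tallies allocations by stratum. The article states neither, and printing the sizes in a journal does not show that recruiters hold them. The list and envelopes are in independent hands, only participants and acupuncturists are named as aware, and the code identities reach the research team only after the analysis is finalised. A recruiter who ignored the strata would do worse: with an assumed 70/30 split between strata, about 20% of allocations reach the 80% mark. This stands as a limit on the figures. It does not remove the weakness, since nothing in the article keeps recruiters unaware, and two strata at one site are easy to follow.

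Second, the 80% mark lies just below the 83.3% of step 2 and so shows the larger blocks in a good light. At 90% the shares are 16% for 2/4 and 5% for 4/6/8, and correct guesses overall fall only from 72% to 68%. This also stands, and it is why withholding the sizes matters as much as enlarging the blocks.

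Third, the analysis model adjusts for baseline values and endocrine therapy status. That removes selection on those variables, but not on motivation or expectation.

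Two stronger readings are tempting, and neither is supported:
- A reader might infer that the second allocation in a block of 2, and the last in a block of 4, is always known. That requires knowing where each block starts. If it were so, (1 + 4/3) / 6 = 39% of allocations would be certain at an equal mix, against the 11% found.
- A reader might take "Participants will receive their envelopes in the order of enrollment to determine their group allocation" to mean a single envelope series that breaks the stratification. The same section states a stratified block design, and how the envelopes are numbered per stratum is a detail an article may leave to the full protocol.

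**Conclusion.** The point holds as a conditional weakness in allocation concealment that arises from a stated design choice. For a recruiter who knows the sizes and tallies by stratum, and an equal mix, about 55% of allocations are predictable with at least 80% certainty, about 11% are certain and about 72% are guessed correctly. The first figure stays above half for any mix with some blocks of 4, up to a probability of 0.6. It is about 48% when two thirds are of size 4 and about 32% when all are.

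The documents do not show that recruiters have this knowledge, nor do they rule it out. They do not show that enrolment has been or will be steered, and no effect on the treatment contrast can be estimated from them. Bias from self-report by unmasked participants is a separate matter, which the Discussion already acknowledges. The selection problem differs in that it can be reduced cheaply.

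**What to change.** Drop blocks of 2 and use randomly varying larger blocks, for example 4, 6 and 8, within each endocrine therapy stratum. Only the independent biostatistician should know the sizes, in a document that recruiting staff cannot see. State in the protocol that staff who screen and enrol are kept unaware of the sizes and, as far as the single site allows, of earlier allocations.

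Under the same assumptions, predictions at 80% or more fall from about 55% to 23% and certain ones from about 11% to 2%. The overall correct-guess rate falls only from about 72% to 68%.

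The cost is a new list before enrolment, or for the remaining participants if enrolment has begun. The largest possible imbalance within a stratum rises from 4/2 = 2 to 8/2 = 4, which is small in a trial of 100 whose model already includes endocrine therapy status.

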### Blinding

2.7

Given the distinct nature of LSM therapy, creating a placebo moxibustion is challenging. Consequently, this study will be conducted as an open-label trial, with both participants and acupuncturists aware of their treatment assignments. To mitigate potential bias, blinding will be maintained for outcome assessors, data managers, and statisticians. During assessments, outcome assessors will use CRFs containing participant names, while both participants and assessors will be instructed to avoid discussing treatment allocation. Once assessments are complete, independent administrative staff overseeing randomization will replace participant names with coded labels, and group assignments will be replaced with anonymized labels. The anonymized dataset will then be provided to data managers and statisticians for analysis. Since statisticians will only have access to the anonymized dataset, they will conduct the analysis without knowledge of treatment group assignments, ensuring unbiased interpretation of results. After data analysis is finalized, the identities associated with the codes will be disclosed to the research team for accurate interpretation of the results.

### Sample size

2.8

To obtain a preliminary estimate of LSM’s efficacy, a pilot study was conducted with 12 participants assigned to each of the two groups, based on the rules of thumb (29). After the 4-week treatment period, ISI scores decreased by 6.82 ± 4.06 points in the LSM group and 3.24 ± 2.38 points in the WC group from baseline. The observed effect size (Cohen’s *d*) was 1.08, which, according to Cohen’s criteria (*d* = 0.2 as small, *d* = 0.5 as medium, and *d* = 0.8 as large), indicates a large effect. Based on these results, the sample size was calculated using the “Two-sample *t*-tests allowing unequal variance” module in PASS software, version 15.0, with a two-tailed alpha of 0.05 and a power of 0.90, while accounting for a 10% expected dropout rate. Previous studies have shown that endocrine therapy is an important risk factor for insomnia in breast cancer patients (9). Therefore, to account for potential heterogeneity in treatment response, the sample size was stratified by endocrine therapy status (yes vs. no). To ensure sufficient statistical power within both strata, the sample size was adjusted to 46 participants per group. Ultimately, considering the importance of using whole numbers for clear communication of results, and to further enhance the statistical power of the study, the sample size per group was rounded up to 50 participants.

### Statistical analysis

2.9

The analysis will be conducted based on the intent-to-treat (ITT) population, defined as participants who complete baseline assessments and have at least one follow-up measurement. The Shapiro–Wilk test will be employed to assess the normality of the data distribution. For continuously measured repeated data, such as ISI scores, PSQI scores, PFS scores, FACT-B scores, and hypnotic medication dosages, a mixed-effects model adjusted for baseline values will be used to compare longitudinal changes from baseline across follow-up time points between groups. The model will include fixed effects for endocrine therapy status (yes or no), time, group, and the interaction between time and group, while treating individual participants as random effects. Given that mixed-effects models can accommodate participants with at least one outcome measurement, no imputation will be performed for missing values in the primary analysis (30).

For non-repeated continuous variables, such as serum biochemical markers and gut microbiota abundance, between-group comparisons will be performed using either the *t*-test or Mann–Whitney *U* test, depending on data distribution. Categorical variables, including treatment response rates and incidence of adverse events, will be analyzed using chi-square or Fisher’s exact tests. Correlation analyses between ISI scores, differential serum biochemical markers, differential metabolites, and key gut microbiota will be performed using Pearson or Spearman correlation coefficients. Missing values for data analyzed using non-mixed effect models will be managed using multiple imputation methods.

For the primary efficacy outcome (the change in the ISI score from baseline to the end of the 4-week treatment period), subgroup analyses will be conducted based on hypnotic medication use (yes, no) and insomnia severity (mild, moderate, severe) to further explore potential variations in the treatment effects of LSM across different subgroups. Additionally, sensitivity analyses will be performed for the primary efficacy outcome. Specifically, if missing values or non-normally distributed data are present, multiple imputation methods will be used to assess the impact of missing data, and generalized estimating equations will be employed as a non-parametric alternative for non-normally distributed data. Pre-specified per-protocol analyses will also be conducted. The per-protocol set will include all participants who completed the intervention and follow-up according to the study protocol. The results of the primary analysis will be compared with those from these sensitivity analyses to assess robustness.

All statistical analyses will be carried out using SPSS (version 26.0) and R (version 4.3.1). Two-tailed significance testing will be applied, with a *p*-value threshold of ≤ 0.05 indicating statistical significance.

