#### Primary efficacy outcome

2.4.1

The primary efficacy outcome will be the change in ISI score from baseline to the end of the 4-week treatment period. The ISI is a validated 7-item self-report measure that has demonstrated strong internal consistency and construct validity for evaluating insomnia severity in cancer patients (20). ISI scores are categorized as follows: 0–7 (no clinically significant insomnia), 8–14 (mild insomnia), 15–21 (moderate insomnia), and 22–28 (severe insomnia) (21). ISI assessments will be conducted at baseline, as well as at weeks 2, 4, 6, and 8 following the start of treatment.

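### The primary mixed model names only a participant random effect, so the week-4 standard error may rest on a variance averaged over weeks 2 to 8

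*Protocol article*

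**What the plan says.** The primary outcome concerns one visit: "The primary efficacy outcome will be the change in ISI score from baseline to the end of the 4-week treatment period" (2.4.1 Primary efficacy outcome). The data in the model come from four: "ISI assessments will be conducted at baseline, as well as at weeks 2, 4, 6, and 8 following the start of treatment".

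For ISI and the other repeated scores, 2.9 Statistical analysis states that "a mixed-effects model adjusted for baseline values will be used to compare longitudinal changes from baseline across follow-up time points between groups". The fixed effects are endocrine therapy status, "time, group, and the interaction between time and group, while treating individual participants as random effects". Participant is the only source of within-person dependence named. The section mentions no random slope, visit-specific variance, residual covariance or robust standard error. It also does not say that residuals are independent with equal variance.

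The primary analysis uses no imputation and relies on this model for missing visits. Among the sensitivity analyses, generalized estimating equations are tied to non-normal data and multiple imputation to missing data.

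The only SDs of ISI change in the article are the pilot week-4 values in 2.8 Sample size: "ISI scores decreased by 6.82 ± 4.06 points in the LSM group and 3.24 ± 2.38 points in the WC group from baseline".

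**The concern.** Read plainly, a participant random effect is a random intercept. With independent, equal-variance residuals it implies one variance for all four visits and one correlation for every pair of visits. The test of the primary outcome is a week-4 contrast, but its SE then comes from all four visits together.

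Equal spread across visits cannot be taken for granted. The response is change from baseline after four sessions (week 2), after all eight (week 4), and two and four weeks after treatment ends (weeks 6 and 8). If response to treatment varies between participants, the spread could be largest at week 4, which is the direction that makes the SE too small.

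At stake are the confidence interval and p-value of the primary result. The same covariance also governs how the observed visits inform a missing week 4. None of the planned sensitivity analyses is triggered by unequal visit variances.

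**Working it through.** **Inputs from the Protocol article.** Pilot week-4 SDs are 4.06 (LSM) and 2.38 (WC), and the mean difference is 6.82 − 3.24 = 3.58. There are 50 participants per arm, allocation is 1:1, and the follow-up visits are weeks 2, 4, 6 and 8.

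**Assumed, because the article does not give them.** The SDs at weeks 2, 6 and 8 are set relative to week 4, and the within-person correlation is 0.6.

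**1. The plan's own figure.**
- Average SD = √((4.06² + 2.38²)/2) = √((16.48 + 5.66)/2) = √11.07 = 3.33.
- Cohen's d = 3.58/3.33 = 1.08, as stated.
- The unequal-variance t-test needs 20 per arm for 90% power (power 0.909; 19 gives 0.893). Allowing for 10% dropout, 20/0.9 = 22.2, rounded up to 23. Two strata give 2 × 23 = 46, as stated.

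The sample size therefore reproduces and is not in dispute here.

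**2. Formulas (complete data, n per arm).**
- True week-4 SE = √(2 × week-4 variance / n) = √(2 × 11.07/50) = 0.666.
- Random-intercept week-4 SE = √(2 × mean of the four visit variances / n).
- Ratio r = √(mean visit variance / week-4 variance). Approximate type I error = 2 × (1 − Φ(1.96 r)).

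**3. Assumed visit patterns.** SDs are relative to week 4. The simulations used 50 per arm and the pilot arm SDs.

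| SD at weeks 2/4/6/8 | Mean squared relative SD | r | Model SE | Type I, formula | Type I, simulated |
|---|---|---|---|---|---|
| 1/1/1/1 | 1.000 | 1.000 | 0.666 | 0.050 | 0.050 |
| 0.8/1/1/1.166 | 1.000 | 1.000 | 0.666 | 0.050 | 0.049 |
| 0.8/1/1.1/1.1 | 1.015 | 1.007 | 0.671 | 0.048 | 0.049 |
| 0.8/1/1/1 | 0.910 | 0.954 | 0.635 | 0.062 | 0.062 |
| 0.85/1/0.9/0.9 | 0.836 | 0.914 | 0.608 | 0.073 | 0.073 |
| 0.75/1/0.8/0.8 | 0.711 | 0.843 | 0.561 | 0.098 | 0.099 |
| 0.6/1/1.2/1.3 | 1.123 | 1.059 | 0.705 | 0.038 | 0.039 |

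For example, in the sixth row (0.5625 + 1 + 0.64 + 0.64)/4 = 0.711 and √0.711 = 0.843, so the SE is about 16% too small. Using the week-4 variance instead gave simulated type I error of 0.049 to 0.052 in all rows. Fits of a random-intercept model by REML gave mean SEs close to the formula: 0.657 v 0.666 (equal), 0.559 v 0.561 (sixth row) and 0.701 v 0.705 (last row).

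**4. A pattern with different shapes in the two arms.** Assumed SDs are LSM 2.5/4.06/3.4/3.0 and WC 1.8/2.38/2.3/2.2. The mean visit variances are 10.82 and 4.76 (sum 15.58). The week-4 variances are 16.48 and 5.66 (sum 22.15, from unrounded values). The ratio is √(15.58/22.15) = 0.84, again about 16% too small. Simulation with 45 per arm gave type I error of 9.8%.

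**5. Unequal arm variances alone.** The first row of the table has the pilot arm SDs at every visit, and its type I error is 0.050. With 40 LSM and 50 WC:
- Pooled variance = (39 × 16.48 + 49 × 5.66)/88 = 10.46.
- Model SE = √(10.46 × (1/40 + 1/50)) = 0.686.
- True SE = √(16.48/40 + 5.66/50) = 0.725.

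The model SE is then about 5% too small. So unequal arm variances matter only if the numbers per arm diverge.

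**The case against.** The strongest objection is that the article never states the residual covariance. A participant random effect does not exclude a residual structure by visit, and a condensed article commonly leaves that detail to the full plan. This stands in part: compound symmetry is the plain reading, not an explicit commitment. But the article does describe the dependence structure, and participant is all it names. If the full plan uses an unstructured covariance, this sentence misdescribes it and should be corrected.

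A reader might infer three stronger things that the document does not support:
- **That the SE is wrong at any difference in spread between visits.** It is wrong only when the week-4 variance differs from the visit average. The second and third rows of the table vary by visit and leave the SE within about 1%.
- **That the pilot SDs of 4.06 and 2.38 show the primary test to be invalid.** At equal arm sizes they do no harm.
- **That inflation to about 10% is to be expected.** That figure comes from patterns chosen to peak at week 4. A growing pattern pushes the other way, and the article gives no visit SDs to decide between them. A small check of 300 fits per scenario that included baseline and stratum gave 7.7% (95% interval 4.9% to 11.3%) for a peak and 3.0% (1.4% to 5.6%) for growth. Those intervals include 5%, so that check is weak on its own.

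It is also fair that at the pilot effect the conclusion is safe: 3.58/0.666 = 5.4 standard errors, with power above 0.999 at 50 per arm. The risk lies in the width of the interval and in the p-value if the true effect is smaller or nil.

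**Conclusion.** The point holds in a limited form. If the stated model is fitted as a random intercept with independent, equal-variance residuals, the primary week-4 SE depends on the spread at weeks 2, 6 and 8. Neither the direction nor the size of the resulting error can be established from the article. The range of about 16% too small to about 6% too large rests on assumed visit SDs, complete data and equal arms, and there is no error when visit variances are equal. It is worth correcting because the primary interval and p-value need not depend on this assumption at all, and no planned sensitivity analysis addresses it.

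**What to change.** In 2.9 Statistical analysis, for ISI and the other repeated scores, replace the random-participant structure with a repeated-measures mixed model that has:
- unstructured covariance over the follow-up visits, common to both arms;
- Kenward-Roger or Satterthwaite degrees of freedom;
- a named fallback with visit-specific variances, such as heterogeneous Toeplitz, if the model does not converge.

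The fixed effects can stay as they are. Arm-specific covariance belongs in a sensitivity analysis, useful mainly if dropout leaves the arms unequal.

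**Cost.** This is a change of wording. For four ISI visits an unstructured covariance has 4 × 5/2 = 10 parameters against 2 for the random intercept, so eight more. With about 90 to 100 participants the loss of precision is negligible. Estimating it separately by arm would take 20 parameters, which is a reason not to make that the primary model.
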